## Discontinuation/Withdrawal of Participants from Study Medication

Each participant has the right to withdraw from the study at any time. In addition, the Researcher may discontinue a participant from the study at any time if s(he) considers it necessary for any reason including:

- Pregnancy
- Ineligibility (either arising during the study or retrospectively having been overlooked at screening)
- Significant protocol deviation
- Significant non-compliance with treatment regimen or study requirements
- An adverse event which requires discontinuation of the study medication or results in inability to continue to comply with study procedures
- Disease progression which requires discontinuation of the study medication or results in inability to continue to comply with study procedures
- Withdrawal of Consent
- Loss to follow up

When a participant stops study medication or withdraws consent, all study data collection will be stopped. Data and samples collected prior to withdrawal will be retained and the reason for withdrawal, if given, will be recorded. Where appropriate, the participant will be asked for a final set of ratings and blood samples and be advised on ongoing treatment, if relevant. If withdrawal is due to an adverse event, the researcher will arrange for follow-up visits or telephone calls until the adverse event has resolved or stabilised. Participants will be asked to return all of the devices they had been given at the beginning of the study as outlined in the devices agreement signed at the start of the study (see appendix M).

## Definition of End of Study

The end of study is the date of the last post-study follow-up of the last participant.

## Description of procedure

***Daily cognitive tasks***. Participants will be asked to complete a battery of neuropsychological tests on a computer. They will also be provided with an iPad with pre-installed apps to enable them to complete short cognitive assessments (Appendix E) plus the PANAS questionnaire twice daily. They will be shown how to use the apps and asked to respond to prompts to complete cognitive assessments for the duration of the study. Data from the apps will be sent wirelessly and electronically to a secured server for analysis.

Participants will be informed that they are able to contact the Research Team during working hours should they have any concerns or if they experience any problems with the iPad or activity monitor(s) (see Appendix F: *Theme 3*).

Imaging interventions: Participants who need optical correction will be asked for details of their current spectacle prescription so that researchers can check whether they will be able to provide MRI/MEG compatible glasses for that prescription (Appendix E).

***Sleep, motor activity and social interactions*.** Participants will be given an activity monitor (GeneActiv wrist-worn accelerometer) and asked to wear it as much as possible from entry into the study until the end of the randomised phase. Participants will be provided with instructions on how to use the monitor and data will be stored on the device itself .

Participants will be given a copy of the Sleep Condition indicator; self-report sleep measure (Espie, 2014), and the Morningness-Eveningness Questionnaire (MEQ) and asked to complete them before wearing the ePatch for 72 hours (see below). Participants will also be asked to keep a sleep diary for the study duration.

***Profile of the calcium signalling system.*** Effects of nicardipine on leucocyte calcium channel expression and calcium signalling will be explored. Participants will be asked to provide blood samples (of approximately 9 teaspoonfuls of blood) pre-calcium treatment at the screening visit and post-calcium treatment at the final visit 2 weeks after randomisation (Appendix G).

***Physiological effects of nicardipine*.** Heart rate and blood pressure will be measured. Participants will also be provided with an e-Patch, shown how to attach it and asked to wear it for a 72-hour period prior to randomisation and 72 hours post-randomisation (Appendix I)**.**

# NICARDIPINE

## Description

Nicardipine will be provided as Cardene SR 30mg capsules. Cardene SR 30mg capsules will be purchased from Oxford Pharmacy Stores. The Department of Psychiatry will (over-)encapsulate Cardene (to mask print on the capsule) and encapsulate matched placebo tablets. Each bottle will be assigned a unique randomisation number to ensure concealment of allocation.

*Nicardipine dose:* Following random allocation (see 8.6), nicardipine/placebo will be given at a dose of 60mg. This will be a stable dose throughout the study period. Participants will be instructed to take the capsules as two separate doses – one 30mg dose after breakfast and one 30mg dose at bedtime*. Nicardipine takes at least 3 days to reach steady state plasma levels.

* Capsules should be taken as near to 12 hours as possible after the previous dose.

## Storage

Nicardipine and placebo will be transferred to the pharmacy at the NIHR-CRF as required. Dispensing will be done by trained staff at the NIHR-CRF. Nicardipine will be stored in a controlled temperature environment and below 25° as per product directions.

## Compliance with Study Medication

Participants will be asked to report adherence to study medication and to return any unused medication. Returned pill counts will be used to provide further tests of adherence.

## Accountability of the Study Medication

All medication will be accounted for by the NIHR-CRF and allocated medication will be recorded on a Drug Allocation Log (DAL) for each participant.

## Concomitant Medication

Participants will be asked to avoid any changes in concomitant medication during the randomised phase as far as possible. Any changes that are made will be recorded.

# SAFETY REPORTING

## Definitions

| **Adverse Event (AE)** | Any untoward medical occurrence in a participant to whom a medicinal product has been administered, including occurrences which are not necessarily caused by or related to that product. |
| --- | --- |
| **Adverse Reaction (AR)** | All adverse events judged by either the Investigator or the Sponsor as having a reasonable suspected causal relationship to an investigational medicinal product qualify as Adverse Reactions. The expression reasonable causal relationship means to convey in general that there is evidence or argument to suggest a causal relationship. |
| **Serious Adverse Event (SAE)** | A serious adverse event is any untoward medical occurrence that:   - results in death - is life-threatening - requires inpatient hospitalisation or prolongation of existing hospitalisation - results in persistent or significant disability/incapacity - consists of a congenital anomaly or birth defect.   Other ‘important medical events’ may also be considered serious if they jeopardise the participant or require an intervention to prevent one of the above consequences.  NOTE: The term "life-threatening" in the definition of "serious" refers to an event in which the participant was at risk of death at the time of the event; it does not refer to an event which hypothetically might have caused death if it were more severe. |
| **Serious Adverse Reaction (SAR)** | An adverse event that is both serious and, in the opinion of the reporting Investigator, believed with reasonable probability to be due to one of the study treatments, based on the information provided. |
| **Suspected Unexpected Serious Adverse Reaction (SUSAR)** | A serious adverse reaction the nature and severity of which is not consistent with the information about the medicinal product in question i.e.:   - in the case of a product with a marketing authorisation, in the summary of product characteristics (SmPC) for that product - in the case of any other investigational medicinal product, in the Investigator’s Brochure (IB) relating to the study in question. |

NB: to avoid confusion or misunderstanding of the difference between the terms “serious” and “severe”, the following note of clarification is provided: “Severe” is often used to describe intensity of a specific event, which may be of relatively minor medical significance. “Seriousness” is the regulatory definition supplied above.

Any pregnancy occurring during the clinical study and the outcome of the pregnancy should be recorded and followed up for congenital abnormality or birth defect, at which point it would fall within the definition of “serious”.

Causality

The relationship of each adverse event to the study medication must be determined by a medically qualified individual according to the following definitions:

*Related:* The adverse event follows a reasonable temporal sequence from study medication administration, cannot reasonably be attributed to any other cause.

*Not Related*: The adverse event is probably produced by the participant’s clinical state or by other modes of therapy administered to the participant.

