## SUSAR Reporting

A serious adverse event (SAE) occurring to a participant should be reported to the REC that gave a favourable opinion of the study where in the opinion of the Chief Investigator the event was ‘related’ (resulted from administration of any of the research procedures) and ‘unexpected’ in relation to those procedures. Reports of related and unexpected SAEs should be submitted within 15 working days of the Chief Investigator becoming aware of the event, using the HRA [report of serious adverse event](http://www.nres.npsa.nhs.uk/docs/forms/Safety_Report_Form_(non-CTIMPs).doc) form (see HRA website).

See Appendix C for a SAE reporting flow-chart.

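### The causality scale in Protocol 10.1 contradicts the adverse reaction definitions beside it and leaves some events without a class, so a suspected serious reaction could miss expedited external reporting

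*Protocol*

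**What the plan says.** Protocol 10.1 (Definitions) contains two sets of causality wording.

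The table of terms treats as adverse reactions those events judged by the investigator or the sponsor as "having a reasonable suspected causal relationship to an investigational medicinal product qualify as Adverse Reactions", and explains this as meaning that "there is evidence or argument to suggest a causal relationship". A serious adverse reaction (SAR) is a serious event "believed with reasonable probability to be due to one of the study treatments", in the reporting investigator's opinion. A SUSAR is a SAR that does not match the product information.

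The Causality text below the table is mandatory: "The relationship of each adverse event to the study medication must be determined by a medically qualified individual according to the following definitions". It offers two classes:

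- The first, *Related*, is worded as follows: "The adverse event follows a reasonable temporal sequence from study medication administration, cannot reasonably be attributed to any other cause".
- The second, *Not Related*, asks instead for a probable cause elsewhere: "The adverse event is probably produced by the participant’s clinical state or by other modes of therapy administered to the participant".

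Several reporting routes then turn on relatedness. Section 10.5 states: "Reports of related and unexpected SAEs should be submitted within 15 working days of the Chief Investigator becoming aware of the event". It adds its own explanation of related, in terms of an event arising from a research procedure, in the Chief Investigator's opinion. The Appendix C flow chart asks whether the event is related to the study drug. Section 10.6 limits yellow card reports to SAEs related to study medication, and promises the Steering Committee chair immediate notice of SARs and SUSARs.

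**The concern.** A causality scale should put into practice the definitions it serves, and every event should fall into one of its classes. This scale appears to do neither. The adverse reaction definition works by suspicion, whereas *Related* works by exclusion of other causes. Between *Related* and *Not Related* lies the ambiguous event, where the drug is plausible and something else is plausible too. Such events are the ones for which a causality rule matters most.

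The setting makes ambiguity likely. Participants are selected for significant mood instability (7.2), and a subset is expected to meet axis I or II criteria (8.3). Axis I disorder and substance use exclude only at the investigator's discretion (7.3). For a psychiatric SAE in particular, the participant's own clinical state will often be a reasonable alternative explanation. At stake is whether a suspected serious reaction gets the right label and is sent outside the study team promptly.

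**Working it through.** No arithmetic is needed to establish the defect. The check sets the causality tests side by side and follows one event through them.

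**1. The tests**

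| Place in Protocol | Term | Test | Must other causes be excluded? |
|---|---|---|---|
| 10.1, table | Adverse reaction | Evidence or argument pointing to the drug | No |
| 10.1, table | SAR (and so SUSAR) | Reasonable probability | No |
| 10.1, Causality | *Related* | Timing fits and no other reasonable cause | Yes |
| 10.1, Causality | *Not Related* | Clinical state or other therapy is the probable cause | Not applicable |
| 10.5 | Related, for the ethics committee report | Event arose from a research procedure, in the Chief Investigator's opinion | Not stated |
| 10.6, yellow card | Related | No definition given there | Falls back on 10.1 |
| Appendix C | Related to study drug | No definition given there | Falls back on 10.1 |

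**2. Is the scale exhaustive?** Take events with plausible timing and a plausible drug cause, and vary the strength of an alternative explanation in clinical state or other therapy.

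- No reasonable alternative: *Related*.
- Alternative probable: *Not Related*.
- Alternative reasonable but not probable: *Related* fails because another cause can reasonably be named. *Not Related* fails because that cause is not probable.

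The third case has no class, although classification is mandatory. The Protocol does not say to which class it defaults.

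**3. Does the scale agree with the definitions above it?** In the third case the alternative is not probable, so the investigator may hold with reasonable probability that the drug is responsible. If the event is serious, it is then a SAR. If it is also unexpected, it is a SUSAR. Yet it is not *Related*. The two parts of 10.1 therefore conflict on the same event.

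**4. Where would that event go?**

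- Internal SAE report and weekly details to the Steering Committee chair (10.3): unaffected, because both cover all SAEs.
- Appendix C: a negative answer to the relatedness question leads away from the expedited report. The chart's connecting lines are not visible in the text at hand, so this assumes that the question controls that route, as its boxes suggest.
- Yellow card (10.6): not triggered if the 10.1 scale is applied.
- Immediate SAR or SUSAR notice to the chair (10.6): missed if the label follows the scale, given if it follows the SAR definition.
- Ethics committee report (10.5): missed if the 10.1 scale supplies the meaning of related; open to the Chief Investigator's judgement if the explanation in 10.5 does.

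**5. Size.** The Protocol gives no SAE rate, so no expected number of misclassified events can be derived. Exposure is limited: 20 planned on nicardipine × 2 weeks = 40 participant-weeks. Assessment is blind, so the scale applies to all 40 randomised, or 40 × 2 = 80 participant-weeks.

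**The case against.** A reader might infer that any serious reaction with another plausible cause disappears from SUSAR reporting, and that the Steering Committee would see too few drug-related events. The documents do not support that.

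- Section 10.3 sends all SAEs to the Research Team within 24 hours and to the Steering Committee chair weekly, with no causality filter; 10.6 repeats that the chair receives all SAEs. The Committee sees the events. What may be lost is the correct label and the immediate notice.
- SUSAR is defined through SAR, which has its own test. An assessor who follows the table in 10.1 could still report the event, and the sponsor may also judge an event to be an adverse reaction.
- Section 10.5 explains related in its own terms and does not refer back to the scale. The ethics committee report may therefore survive.
- Section 10.3 has the psychiatrist and then the Chief Investigator or delegate assess relatedness, so a single narrow reading need not decide the matter.
- The *Related* sentence lacks a conjunction. Reading its two parts as jointly required is natural, but the text is visibly defective.

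It is also tempting to use the symptoms that 10.2 lists for nicardipine, such as headache and dizziness, to show the scale of the problem. They are mostly non-serious and say nothing about missed SUSARs. In 10.2, moreover, being related is the reason for not recording an event routinely, so a narrow *Related* would not reduce recording there.

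All of this limits the consequence. It does not remove the contradiction: whether an event is reported would depend on which part of the Protocol the assessor applies, and the scale is the part worded as mandatory.

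**Conclusion.** The concern stands in a limited form. The mandatory scale in 10.1 is stricter than the adverse reaction and SAR definitions beside it, and it has no class for an event with a reasonable but not probable alternative cause. Such an event, if serious and unexpected, could be a SUSAR by definition and yet miss the Appendix C expedited report, the yellow card and the immediate notice to the chair. Loss of the 10.5 report is possible but not established.

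The conclusion assumes that the two parts of the *Related* sentence are both required, and that Appendix C and the yellow card rule take their meaning of related from 10.1 because they give none of their own. The number of affected events cannot be estimated and, with this exposure, may be small or zero. The point deserves correction because the ambiguous serious event is the one the rule handles worst and because the remedy is cheap. It does not show a failure of all safety oversight.

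**What to change.** Use one exhaustive causality threshold throughout the Protocol:

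- In 10.1, define *Related* as a reasonable possibility that study medication caused or contributed to the event, even when other causes are possible, and *Not Related* as no reasonable possibility.
- Align the SAR wording in the 10.1 table with that threshold. Otherwise reasonable probability remains as a second standard.
- Align the explanation of related in 10.5 with it as well. If events caused by other research procedures are meant to stay reportable there, say so separately.
- State that the relatedness questions in Appendix C and the yellow card rule in 10.6 use the 10.1 definition.

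Changing the two scale definitions alone would leave the SAR and 10.5 wordings unreconciled. The cost is a wording amendment, with its sponsor and ethics approval, and possibly a few more expedited reports. No extra assessment step is created, since 10.3 already has the Chief Investigator or delegate assess each reported SAE.

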## Procedures for Recording Adverse Events

Nicardipine has been widely used at the dose planned to be used in the study and therefore has a well-documented safety profile. Symptoms of headache, upset stomach, dizziness or light headedness, excessive tiredness, flushing, numbness, fast heartbeat and muscle cramps, which can occur at therapeutic levels of nicardipine will be monitored at each assessment visit. adverse events (AEs) that are considered related to nicardipine will not therefore be routinely recorded. Recording will only be required for non-serious AEs that are of longer duration or greater severity than would be expected based on the information in the SmPC. For these ARs, the information recorded on the Study-CRF will include a description of the event, the date of onset and end date, severity (1 = mild, 2 = moderate, 3 = severe), assessment of relatedness to study medication, other suspect drug or device and action taken. Follow-up will continue until either resolution or the event is considered stable.

It will be left to the Investigator’s clinical judgment to decide whether or not an AE is of sufficient severity to require the participant’s removal from medication. A participant may also voluntarily withdraw from medication due to what he or she perceives as an intolerable AE. If either of these occurs, the participant will be asked to undergo an end of study assessment and be given appropriate care under medical supervision until symptoms cease, or the condition becomes stable.

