## Visit 3 – Final visit:

At approximately 2 weeks post-randomisation participants will be asked to attend a final study visit. At this visit, vital signs will be checked, and ECG and blood samples will be repeated. Participants will also complete a second battery of cognitive tasks. All equipment will be returned at this visit including medication bottles and any remaining medication. A post-treatment MRI scan and MEG scan will be done. If possible, post randomisation scans and the final week 2 visit will be carried out on the same day. If this is not possible due to scanner availability, separate visits will be scheduled at the convenience for the participant.

At this visit checks of adherence and for adverse events will be carried out.

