## 8.6. Post-study follow-up

Participants will be contacted within a fortnight of study completion, usually by phone, following cessation of study treatment to review the status of any reported Adverse Events and to check for any unreported AEs.

Please see Appendix B for a schedule of procedures during the study duration.

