## Reporting Procedures for Serious Adverse Events

SAE reporting will cover the period from randomisation and throughout tapering phase until the study nicardipine/placebo has been stopped.

All SAEs must be reported to the Research Team within 24 hours of the researcher becoming aware of the event. The psychiatrist will be asked to complete an SAE Form with the information available at the time of initial reporting and his/her opinion of relatedness and expectedness. S(he) will be asked to supplement this with additional information as it becomes available.

Receipt of an initial SAE report by the OxCaMS RA or NIHR-CRF Lead Nurse for OxCaMS will be acknowledged within 1 working day of receipt and the CI (or delegate) will make an immediate assessment of relatedness and expectedness. The CI will continue to review supplementary information as it is received.

The Chair of the Trial Steering Committee (see 10.6) will be sent details of all SAEs for review by the Committee weekly.

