# Appendix B: Schedule of Procedures

| Attendance number | **1** | **2** | **3** | **4** |
| --- | --- | --- | --- | --- |
| Timeline (days) | **0** | **14** | **28** |  |
| Window (days) |  | **±2** | **±2** |  |
| Informed consent | ✓ |  |  |  |
| Demographics | ✓ |  |  |  |
| Diagnosis (MINI) | ✓ |  |  |  |
| Medical history | ✓ |  |  |  |
| Physical examination | ✓ | ✓ |  |  |
| ECG | ✓ |  | ✓ |  |
| Vital signs and BMI | ✓ | ✓ |  |  |
| Eligibility assessment | ✓ | ✓ |  |  |
| Follow-up call |  |  |  | ✓ |
| Personality disorder screen | ✓ |  |  |  |
| ADHD screen | ✓ |  |  |  |
|  |  |  |  |  |
| Neuropsychological tests | ✓ |  | ✓ |  |
| Randomisation |  | ✓ |  |  |
| True Colours | **✓** Weekly | | |  |
| PANAS | **✓** Daily | | |  |
| Cognitive tests | **✓** Daily | | |  |
| Carry activity monitor | **✓** Daily (with regular data downloads) | | |  |
| Concomitant medications | ✓ | ✓ | ✓ |  |
| Dispensing study drugs and pill count |  | ✓ | ✓ |  |
| Adverse Event check |  | ✓ | ✓ | ✓ |
| MEG |  | ✓* | ✓ |  |
| MRI |  | ✓* | ✓ |  |
| Sleep questionnaire | ✓ | ✓ | ✓ |  |
| Sleep Diary card commenced | ✓ | ✓ |  |  |
| Sleep Diary card completed & returned |  |  | ✓ |  |
| ePatch** | ✓ | ✓ |  |  |
| Portable blood pressure monitor*** |  | ✓ |  |  |
| Blood tests | ✓ |  | ✓ |  |
| Devices returned |  |  | ✓ |  |

- *MEG and MRI scan prior to taking any study medication.
- ** Wear for 72 hours
- *** Participants to record blood pressure once daily throughout two-week randomisation phase

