# Appendix C: SAE Reporting Flow Chart

**Adverse event**

**Adverse Event**

**No further action**

**Related to IMP?**

**Serious? (See box)**

**Expedited report to REC and Sponsor within:
 - 7 days if fatal/life-threatening, - 15 days if not**

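### Section 10.2 leaves drug-typical adverse events out of routine recording in both arms, and the SAE window, dose wording and expedited clocks contradict other parts of the protocol

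*Protocol*

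**What the plan says.** **Recording of non-serious events.** Section 10.2 argues from the drug's known safety profile that "adverse events (AEs) that are considered related to nicardipine will not therefore be routinely recorded". It continues: "Recording will only be required for non-serious AEs that are of longer duration or greater severity than would be expected" from the SmPC. Events that qualify go on the Study-CRF with description, dates, severity and relatedness. The same paragraph lists expected symptoms, including headache, dizziness, tiredness and flushing, and says they are monitored at assessment visits. It does not say that the answers are recorded. Section 10.1 (Causality) requires a relatedness judgement for every adverse event.

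**Serious events.** Section 10.3: "SAE reporting will cover the period from randomisation and throughout tapering phase until the study nicardipine/placebo has been stopped". Section 8.6 has participants contacted within a fortnight of completion, "following cessation of study treatment to review the status of any reported Adverse Events and to check for any unreported AEs". Section 6.5 and attendance 4 in Appendix B provide for the same contact, and section 8.12 ends the study at the last such contact. The synopsis gives follow-up as 1 week.

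**Expedited reports.** Section 10.5: "Reports of related and unexpected SAEs should be submitted within 15 working days of the Chief Investigator becoming aware of the event". The Appendix C flow chart sets the limit for reports to the REC and sponsor at "7 days if fatal/life-threatening, - 15 days if not".

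**Dose wording.** Section 9.1 describes a dose that stays stable throughout. Section 10.3 mentions a tapering phase. The section on the nicardipine card provides for replacing the card if the dose changes.

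**Vital signs.** The "Vital signs and BMI" row of Appendix B is ticked at attendances 1 and 2 only. Section 6.4 says of the final visit: "At this visit, vital signs will be checked, and ECG and blood samples will be repeated". Section 8.5 also repeats pulse and blood pressure there.

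**The concern.** Whether a non-serious event is written down depends on an opinion about its cause and on a comparison with the SmPC. Both filters select against events typical of the drug. An event never entered on the CRF cannot be recovered by any later analysis plan, so this is not a detail that can be left to the SAP.

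Two consequences bear on the study's own aims. Section 4.2 makes variability in daily cognitive tasks the main focus and explains that mood is measured so that the drug effect can be seen free of it. Dizziness and tiredness are listed as expected symptoms and could plausibly change task scores by another route. Flushing or headache could suggest allocation to a participant or assessor. Without records by arm, neither possibility can be looked at.

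The serious-event rules raise a different problem: staff following one section would breach another, or would not know whether a duty applies.

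**Working it through.** The protocol gives no adverse event rates, so there is no stated figure to reproduce. The check is mainly a comparison of text, with two small calculations for scale.

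**1. What the recording rule covers**

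- Judged related and within SmPC expectation: not routinely recorded (10.2).
- Non-serious and beyond SmPC expectation in duration or severity: recorded with full detail (10.2).
- Listed expected symptoms: asked about, with no recording rule (10.2).
- Judged unrelated: unclear. The requirement sentence speaks of non-serious AEs in general, while the next calls the same events ARs.
- Any AE: relatedness must be determined (10.1), although under 10.2 many of these judgements would have nowhere to be entered.

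The test of relatedness is itself not fixed. The causality definition in 10.1 requires that no other cause reasonably explains the event; the AR definition in the same section asks only for a reasonable suspicion.

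**2. Effect on a comparison by arm**

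Section 8.7 keeps assessors blind, so take the share *f* of a drug-typical symptom left unrecorded to be the same in both arms. Then

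recorded count = 20 × true rate × (1 − *f*).

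With assumed rates of 30% and 10%, the true counts are 20 × 0.30 = 6 and 20 × 0.10 = 2. The recorded counts fall from 6 vs 2 (*f* = 0) through 3 vs 1 (*f* = 0.5) to 0 vs 0 (*f* = 1). The documents do not give *f*. The recorded difference shrinks in proportion to 1 − *f*.

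**3. What full recording could support**

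Inputs: 20 per arm (section 11.1), two-sided 0.05, assumed rates *p*₁ and *p*₂ with mean *p̄*. Normal approximation:

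power = Φ{ [ |*p*₂ − *p*₁| − 1.96 √(2*p̄*(1−*p̄*)/20) ] / √[ (*p*₁(1−*p*₁) + *p*₂(1−*p*₂))/20 ] }

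For 10% vs 30%: (0.20 − 1.96 × 0.1265) / 0.1225 = −0.39, so power is 0.348.

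| Assumed rates | Power |
| --- | --- |
| 10% vs 20% | 14% |
| 10% vs 30% | 35% |
| 10% vs 40% | 60% |
| 10% vs 50% | 81% |

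With 0 events in 20, the one-sided 95% upper limit is 1 − 0.05^(1/20) = 13.9%. Complete records would therefore describe the arms, not test them.

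**4. The SAE window**

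Treatment lasts 14 days. Assume that drug stops at day 14 and that follow-up is counted from there.

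- Synopsis, 1 week: 7 of 14 + 7 = 21 days lie after the window closes.
- Section 8.6, up to a fortnight: up to 14 of 14 + 14 = 28 days.

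An SAE that begins on treatment and is learned of at the call is inside the covered period. One that begins after the last dose is not, although the call is designed to find it and the study is still open.

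**5. The expedited clocks**

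Fifteen working days is 3 weeks, or 21 calendar days. For a fatal or life-threatening related and unexpected event, section 10.5 allows 21 days where Appendix C allows 7, three times as long. For other such events the two agree only if the 15 days in Appendix C are working days, which it does not say. Both routes lead to the REC, so the conflict is direct.

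**6. Dose wording**

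Stable throughout (9.1), tapering (10.3) and a card replaced on dose change (nicardipine card) cannot all describe the same treatment phase.

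**The case against.** The strongest reply is that reduced recording is a reasoned choice. The drug is widely used, section 10.2 gives that as its reason, and section 5 lists no safety or tolerability objective. The rule says routinely, keeps an exception for events beyond SmPC expectation, and sits alongside AE checks at attendances 2, 3 and 4. Sections 8.11 and 10.2 provide follow-up or care, until events resolve or stabilise, for participants who stop because of an AE. All of that stands, and it limits the point to incomplete recording. It does not answer the missing recording rule for symptoms that are already being asked about.

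A reader might infer more than the documents support:

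- **That the trial promises a tolerability comparison and fails it.** It promises none, and step 3 shows that 20 per arm would give only a coarse one.
- **That mild and moderate headache would appear as 0 vs 0.** This needs every case to be judged related, within SmPC expectation and not prolonged. A long-lasting mild headache could qualify for recording.
- **That serious events after treatment cannot be captured.** The follow-up contact can find them, and section 10.6 sends all SAEs to the committee chair with no cut-off. What is missing is a clear duty under 10.3.
- **That half the time from randomisation falls outside the SAE window.** That uses section 8.6 alone; the synopsis gives one third.
- **That on-treatment vital signs are lost.** Sections 6.4 and 8.5 require them, blood pressure is recorded at home daily, and only the Appendix B tick is absent.

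**Conclusion.** The concern holds as a recording gap together with internal contradictions; it should be fixed. Under section 10.2, symptoms typical of nicardipine are under-recorded in both arms, so counts by arm are incomplete and their possible influence on cognitive scores or blinding cannot be examined. How much is lost cannot be stated, because the protocol gives neither event rates nor the share that would be filtered out. This does not show that the primary comparison is invalid.

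The SAE window leaves about 1 week (synopsis) to 2 weeks (section 8.6) after the last dose with no clear reporting duty under 10.3, assuming drug stops at day 14. The clock conflict is plain for fatal or life-threatening events: 7 days against about 21. The dose wording is contradictory on its face. The Visit 3 vital-signs tick is a minor schedule inconsistency.

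**What to change.** - **Section 10.2 and CRF:** record the already-monitored symptoms and all other AEs in both arms, whatever the judged relatedness, with severity and dates, from randomisation to the follow-up contact. Tabulate by arm without formal testing. A tick-list for the named symptoms is enough. Use one definition of relatedness, and one term for the events being recorded.
- **Section 10.3:** align the SAE reporting period with the follow-up contact, and reconcile the synopsis and section 8.6 on when that contact takes place.
- **Sections 9.1 and 10.3 and the nicardipine card text:** reconcile the statements on stable dose, tapering and dose change. Which is correct is for the investigators to settle.
- **Section 10.5 and Appendix C:** reconcile into one expedited clock, stating whether days are calendar or working days.
- **Appendix B:** bring the vital-signs row into line with sections 6.4 and 8.5.

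The cost is protocol wording and a few more CRF lines for 40 participants. The symptoms are already asked about at existing visits, and the follow-up contact is already scheduled, so no visit is added.
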